### Data management and confidentiality

All data will be collected using computer-based data acquisition programs. This data will be securely stored in a restricted-access folder on Box.com, an encrypted, cloud-based storage system. Any physical content (e.g., pre-screening questionnaires and informed consent documents) will be stored in a locked drawer in a restricted-access office. These documents will not be shown to any individual other than the investigators or the participants. Each participant will be assigned a participant number and all data files will be named according to the number such that the identity of the participants will only be apparent to observers other than the investigators. Important protocol modifications prior to the completion will be communicated with the trial registry and the journal of publication. The confidentiality of the personal information will be protected by the principal investigator. All investigators will have access to the final dataset. A data monitoring committee is not needed as minimal risk applies to this protocol.

### Safety assessment

To minimize any risk of falls, a spotter will be positioned behind the participants and cushion mats will be positioned around them during the land exercise session. There is no risk of falls during the aquatic exercise session. However, a spotter, who is certified in CPR, Basic Life Support, or Lifeguard, will be positioned behind the participants during the aquatic exercise session. During the testing sessions, participants will wear a harness, which is secured to the ceiling to prevent them from falling in case they fail to recover balance. Any adverse events or unintended effects will be monitored throughout the study, follow-up, and four weeks after the intervention and discussed in the final registered report research article.

### Statistical analysis

Dependent variables included in the statistical analyses will be: 1) hand contact time during REACH; 2) foot-off time during STEP; 3) foot contact time during STEP; 4) rapid response accuracy during RANDOM; 5) mini-BESTest score of REACH; 6) mini-BESTest score of STEP; 7) mini-BESTest score of RADOM. There are two independent variables including the groups (AE vs. LE) and time (pre vs. post vs. follow-up).

The baseline differences in demographic data and all dependent variables between AE and LE groups will be analyzed using independent samples t-tests for data with a normal distribution and using the non-parametric Mann-Whitney U-test for data without normal distribution. On confirming the assumptions of the normal distribution (Kolmogorov–Smirnov test) and homogeneity of variances (Levene’s test), dependent variables will be compared using 2 (group: AE, LE) × 3 (time: pre, post, follow-up) repeated-measures (RA) analysis of variance (ANOVA) with group as a between-group factor and time as a within-group factor. If baseline differences of the dependent variables occur, baseline values will be included as covariates. If the assumptions are violated, Kruskal-Wallis one-way ANOVA will be used for nonparametric variables. In addition, post-hoc analyses will be conducted using Tukey post hoc test or Mann-Whitney U test. The meaningfulness of statistical differences will be reported using Cohen’s d effect sizes (ES) and confidence intervals (95%) for the parametrical variables and probability of superiority for dependent samples (PS_dep_) for the nonparametric variables [41]. Alpha will be set *a priori* at .05 for all statistical analyses. Missing data will be handled using multiple imputation, and all statistical analyses taking an intention-to-treat approach will be conducted with SPSS version 25 (SPSS Inc., Chicago, IL, USA).

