### Sample size calculations

A power analysis was conducted using G*Power software package (Version 3.1.9.7, Kiel University, Germany). Using results from previous work [26], an a-priori power calculation (α = 0.05, and 1-β = 0.80) determined that 38 participants (19 per group) will be required to determine significant intergroup differences based on large effect size (Cohen’s d > 0.8). Berg Balance Scale (BBS) score data from an AE and LE group were extracted for the analysis as (1) there was no study comparing the effects of AE and LE on any measures of reactive balance and (2) BBS is commonly considered to be the gold standard in testing functional balance and measuring fall risk in older adults [32]. Considering an approximately 15% dropout rate, a total of 44 participants (22 in each group) will be expected to enter the study.

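### Assumption tests choose the analysis outcome by outcome, so chance alone could send about 8–38% of sound continuous outcomes to a test with no group-by-time term

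*Protocol article*

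**What the plan says.** In the protocol article, Statistical analysis, the main analysis is a two-group by three-time repeated-measures ANOVA for each of seven dependent variables. Its use depends on two preliminary tests: it goes ahead "On confirming the assumptions of the normal distribution", by a Kolmogorov–Smirnov test, and of equal variances, by Levene's test. If either fails, the section directs: "If the assumptions are violated, Kruskal-Wallis one-way ANOVA will be used for nonparametric variables". Alpha is set "at .05 for all statistical analyses".

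The effect measure switches with the test. Cohen's d with a 95% confidence interval goes with the parametric branch, and a probability of superiority for dependent samples goes with the nonparametric branch.

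The Problem statement and the Abstract give the hypothesis: AE participants will improve more on the reactive balance test than LE participants. Under Outcome measurement, each mini-BESTest item is scored from 0 to 2.

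**The concern.** The rule lets the trial data decide, variable by variable, which analysis supports each claim. A two-by-three layout offers six cells to test for normality and three time points to test for equal variance. Even when the assumptions hold exactly, the chance that something is flagged is therefore well above 5%.

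The consequence is larger than a swap between near-equivalent tests. The ANOVA contains the group-by-time interaction, which is the hypothesis. A one-way Kruskal-Wallis test compares groups on a single factor. It has no interaction, and it cannot carry the baseline covariates that the same section plans to add when baselines differ. A false alarm thus changes the question answered as well as the p-value. The outcomes could also end up under different analyses, with different effect measures, for no substantive reason.

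**Working it through.** The protocol states no false-alarm rate for this rule, so there is no planned figure to reproduce.

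**Inputs from the protocol article**
- Level of each test: 0.05 (Statistical analysis). That this also covers the assumption tests is my reading.
- Sample size calculations: "38 participants (19 per group) will be required to determine significant intergroup differences", and "a total of 44 participants (22 in each group) will be expected to enter the study". So n is 19 or 22 per arm.
- Cells: 2 × 3 = 6 for normality; 3 time points for Levene.
- Outcomes: seven, of which three are mini-BESTest scores. That leaves 7 − 3 = 4 continuous ones: hand contact, foot-off and foot contact times, and rapid response accuracy.

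**Assumptions, because the protocol is silent**
- Kolmogorov–Smirnov (KS) variant: corrected for an estimated mean and SD (Lilliefors), or uncorrected.
- Level of testing: per cell or pooled over arms; all time points or one.
- Levene's test: mean-centred or median-centred.
- Correlation between visits: 0 to 0.9.

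**Step 1. Chance of at least one false alarm in k independent tests: 1 − 0.95^k**
- k = 9 (6 KS + 3 Levene): 1 − 0.630 = 37.0%
- k = 6 (3 pooled KS + 3 Levene): 1 − 0.735 = 26.5%
- k = 3 (one time point, 2 KS + 1 Levene): 1 − 0.857 = 14.3%
- k = 2 (one time point, 1 KS + 1 Levene): 1 − 0.9025 = 9.75%

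**Step 2. Simulation with exactly normal, equal-variance data** (20,000 trials per setting, 19 or 22 per arm, visits correlated)

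| Reading of the rule | Mean-centred Levene | Median-centred Levene |
|---|---|---|
| 6 corrected KS + 3 Levene | 33–38% | 31–35% |
| 3 pooled corrected KS + 3 Levene | 22–28% | 20–24% |
| One time point, 2 corrected KS + 1 Levene | 14–15% | – |
| One time point, 1 corrected KS + 1 Levene | about 10% | – |
| 6 uncorrected KS + 3 Levene | 11–16% | 8–12% |

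Correlation between visits lowers the rate only slightly: the 6 + 3 reading gives about 35% at a correlation of 0.8 and 33% at 0.9. Uncorrected KS fires in about 0.1% of outcomes or fewer, so in the last row almost all diversion comes from Levene. Uncorrected KS with a single Levene test was not simulated; by the same logic it would sit near Levene's nominal 5%.

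**Step 3. At least one of the four continuous outcomes diverted: 1 − (1 − p)^4, if independent**
- p = 0.08: 1 − 0.716 = 28%
- p = 0.37: 1 − 0.158 = 84%

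The outcomes are not independent, since foot-off and foot contact come from the same step. Allowing for correlation between outcomes at the 37% reading gave 81–84%.

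**Step 4. What a diverted outcome loses**
- ANOVA branch: group, time and group-by-time terms, and baseline covariates if needed.
- Kruskal-Wallis branch: one factor, no interaction and no covariates.

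Only the first branch, as written, tests whether AE improves more than LE.

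**The case against.** The switch is stated in advance, and the Blinding section says that the assessor who analyses the data is blinded. This is therefore not free choice after the event. That stands, but it guards against deliberate selection and not against selection by noise.

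The number of tests and the KS variant are details that an analysis plan may fix. That also stands, and it is why the size is a range and not a single figure. The data-driven switch itself is in the protocol.

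If Kruskal-Wallis were run on change scores, it would still compare AE with LE on improvement. That is fair, but the listed dependent variables contain no change scores and the section does not say so.

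A reader might infer two stronger points, and neither is supported.

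- **That the rule misses most of the skew it is meant to catch.** At skewness about 1, corrected KS detects only about 15–21% in a single cell. The 33–38% diversion figure, however, counts any of nine tests. Counted that way, the rule flags about 66–78% of such outcomes, and 89–96% at skewness 1.5–1.75. With uncorrected KS most skew is missed, but false diversion then falls to 8–16%. High false diversion and poor skew detection do not belong to the same reading, except for mild skew (about 0.6), where the nine-test rule misses roughly half.
- **That the 0.05 level is not held.** Simulating the two-stage rule with no group effect, with Kruskal-Wallis applied to either the change or the post value, gave type I error of 4.9–5.1% for normal and 4.8–5.2% for lognormal data. The fallback's target is assumed here, but nothing in the documents shows inflation.

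**Conclusion.** The concern holds in a limited form. The protocol makes the analysis of each outcome depend on preliminary test results. Under the readings examined, about 8–38% of continuous outcomes that fully meet the ANOVA assumptions would be moved by chance to a test that, as written, does not address the hypothesis. The figure is about 37% for six corrected KS plus three Levene tests.

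It applies to at most four of the seven outcomes. For the three mini-BESTest outcomes normality is implausible from the outset, so diverting them would not be a chance event and no test is needed to choose their analysis.

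The size rests on the assumption tests being run at 0.05, on the KS variant and level of testing, and, to a small degree, on the correlation between visits. The harm is loss or change of the question tested. Loss of error control has not been shown, and no loss of power has been computed.

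**What to change.** Remove the KS and Levene tests as a decision rule. Before unblinding, name one analysis per outcome that always estimates the AE–LE difference in change:

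- For the three times and rapid response accuracy, keep the planned group-by-time linear model, with a transformation if one is specified in advance.
- For the three mini-BESTest outcomes, specify an ordinal model or a rank or permutation comparison of change.
- Use residual checks descriptively, and report any alternative analysis as sensitivity only.

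The choice among a transformation, an ordinal model and a permutation test belongs to the sponsor; the documents do not compel any one of them. What matters is that it is made in advance and keeps the AE–LE difference in change as the target.

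The cost is a paragraph of wording and no new data. Diversion by the assumption tests becomes zero by construction. The small downside is giving up the option to switch tests once the data are in.

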Hence, the current study aims to compare measures of reactive balance control after a single bout intervention on land and in chest-deep water. There have been several studies presenting greater enhancements in dry-land balance performance, specifically in static and proactive balance measures, such as Berg Balance Scale [26], 8-Foot Up and Go Test [27], and Functional Reach Test [28] following AE versus land exercise (LE) in healthy older adults. As none of the previous trials included any measures of reactive balance, the current study will specifically focus on improvements in reactive balance capacity after a single bout intervention. During aquatic exercises, water resistance produces overload during movements, and hydrostatic pressure constantly facilitates sensory awareness and motor functions. Further, the confidence level is augmented in the safer aquatic environment, which in turn increases variability in movement systems and maximizes neuromuscular adaptations. Thus, we hypothesize that participants in an AE group will present greater improvements (e.g., more accurate and rapid responses) during the reactive balance assessment compared to those in a LE group. The greater improvements will be demonstrated by faster response speed (i.e., shorter reaction time), greater accuracy alongside faster response speed (e.g., higher rapid response accuracy), and greater quality of response (e.g., higher mini-BESTest score). The Mini Balance Evaluation System Test (mini-BESTest) is a comprehensive clinical balance assessment, which evaluates four different balance control systems. This tool is commonly used by clinicians and practitioners and well known to be advisable to identify the disordered systems underlying balance control and design specific rehabilitation approaches in varied age and patient populations [29]. In this study, the second section (Reactive Postural Control) will be utilized to score the quality of compensatory balance responses.

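### Baseline adjustment depends on a baseline test and the baseline stays a response level, which costs power at low to moderate pre-post correlation and leaves no clear treatment-effect estimate

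*Protocol article*

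**What the plan says.** All of this is in the Statistical analysis section of the protocol article unless another section is named.

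- **Baseline tests.** Baseline differences in demographics and in all seven dependent variables "will be analyzed using independent samples t-tests for data with a normal distribution", with Mann-Whitney for the rest. Alpha is set "at .05 for all statistical analyses".
- **Adjustment rule.** "If baseline differences of the dependent variables occur, baseline values will be included as covariates".
- **Model.** "There are two independent variables including the groups (AE vs. LE) and time (pre vs. post vs. follow-up"). These enter a 2 x 3 repeated-measures ANOVA "with group as a between-group factor and time as a within-group factor". Nothing takes the pre level out of the time factor when baseline becomes a covariate.
- **Follow-up tests.** "post-hoc analyses will be conducted using Tukey post hoc test or Mann-Whitney U test". The contrast to be estimated is not named.
- **Hypothesis (Problem statement).** "participants in an AE group will present greater improvements".

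The rule does not use the word significant. The baseline tests just before it and the blanket alpha supply the only criterion given, so I read it as a test at .05.

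**The concern.** In a randomised trial any baseline gap is due to chance, so a baseline test says nothing useful about whether to adjust. What matters is how strongly baseline predicts the later values. Making adjustment depend on the test means the covariate is almost never used, and seven outcomes can end up with different models for chance reasons.

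The role of the baseline level is a second difficulty. In the default model, treatment cannot affect the pre level, yet that level counts towards the group main effect. In the triggered model, pre is both a response and its own predictor, so its adjusted group difference is exactly zero.

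At stake are precision in a 44-person trial sized for a large effect, and a reported estimate that a reader can take as the effect of exercising in water rather than on land.

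**Working it through.** **Inputs from the document.** 19 per arm required and 22 per arm recruited, with a large effect of d > 0.8 (Sample size calculations); alpha .05; seven outcomes; simple randomisation (Randomization and allocation concealment). The plan gives no figure of its own on this point to reproduce, and its sample size enters only as an input.

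**Assumptions.** Two-sided tests (sidedness is not stated); d = 0.8 at both post and follow-up; SD 1; the same correlation rho between any two visits, shown from 0.3 to 0.8.

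**1. How often the rule fires.** Under randomisation it fires for 5% of outcomes. For at least one of seven, if they were independent: 1 - 0.95^7 = 0.30. The gap needed is t(.975, 2n - 2) x sqrt(2/n), which is 0.658 SD at n = 19 and 0.608 SD at n = 22. The standard error of the gap at n = 19 is sqrt(2/19) = 0.324, so the mean absolute gap is about 0.26 SD. Per outcome, gaps from 0.3 SD up to the threshold arise with probability 0.31 (n = 19) or 0.28 (n = 22) and do not trigger the covariate.

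**2. Power of the planned procedure.** Simulation, 5,000 trials per scenario, n = 19 per arm. The Monte Carlo standard error is at most sqrt(0.25/5000) = 0.7 points.

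| rho | Interaction, never adjusted | Interaction, plan's rule | Main effect, plan's rule | ANCOVA, mean of post and follow-up |
|---|---|---|---|---|
| 0.3 | 54.9% | 55.6% | 62.0% | 89.3% |
| 0.5 | 69.9% | 70.6% | 52.1% | 91.9% |
| 0.7 | 90.4% | 90.7% | 44.8% | 97.5% |
| 0.8 | 98.3% | 98.4% | 42.7% | 99.5% |

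The conditional rule adds at most 0.7 points to the interaction test.

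**3. Where the gap comes from.** The interaction is a 2-df test and the ANCOVA a single contrast, so not all of the gap is due to adjustment. Like for like, by normal approximation:

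- Mean of the later visits minus pre, variance (1 + rho)/2 + 1 - 2rho: 67%, 81%, 96%, 99% at rho = 0.3, 0.5, 0.7, 0.8.
- ANCOVA of the same mean, variance (1 + rho)/2 - rho^2: 91%, 94%, 98%, nearly 100%.
- One visit alone, change score, variance 2(1 - rho): 55%, 69%, 89%, 97%.
- One visit alone, ANCOVA, variance 1 - rho^2: 73%, 81%, 93%, 98%.

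**4. What each term does with a baseline gap.** A change from pre subtracts the whole gap, while only rho x gap is expected to persist. The interaction contrasts therefore carry a conditional bias of rho x gap - gap = -(1 - rho) x gap. At rho = 0.5 and a gap of 0.6 SD that is -0.3 SD. The main effect leaves the gap in, with weight (1 + 2rho)/3.

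**5. Size of the group main effect.** (0 + 0.8 + 0.8)/3 = 0.53 SD. The simulation gave 0.53 to 0.54 both without the covariate and with it.

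**6. Type I error (simulated with d = 0).** Interaction under the plan's rule: 4.3%, 4.3%, 4.6%, 5.0% across the four correlations. Main effect: 3.1%, 2.8%, 2.7%, 2.0%.

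**The case against.** The strongest reply is that the hypothesis concerns greater improvement. That is the group-by-time interaction, and the interaction already uses the baseline by differencing. Much of this stands, and it rules out several stronger readings:

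- A reader might infer that chance imbalance goes uncorrected throughout. It does not: the interaction subtracts the gap and, if anything, over-corrects it. Only the main effect leaves it in.
- A reader might infer that the trial's treatment effect is diluted by a third. That applies to the group main effect, which the article does not name as its test. In the rare triggered branch the main-effect estimate still shrinks, but its p-value equals that of the ANCOVA.
- A reader might compare ANCOVA with a post-only t-test (67% power at n = 19 and d = 0.8). The plan contains no such test.
- Pre and post measurements bracket a single session, so a high correlation cannot be excluded. At 0.8 the power loss nearly vanishes.
- Sphericity handling is not mentioned, but an article may leave that to the analysis plan.

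What does not stand is that this rescues the plan. The article does not name the interaction as the deciding test either. At low to moderate correlation the interaction loses substantial power. An omnibus interaction is not an estimate, and the named follow-up does not supply one: Tukey's procedure adds nothing for a two-level group factor and does not give the baseline-adjusted AE-LE difference at post or follow-up.

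**Conclusion.** The concern holds as one of efficiency and clarity. The adjustment rule is stated in the article, so it is not a detail left to an unseen document. It leaves about 95% of analyses unadjusted. Against an always-adjusted ANCOVA of the two later visits, the interaction test gives up about 34 points of power at a correlation of 0.3 (89.3 - 55.6), 21 at 0.5 (91.9 - 70.6), 7 at 0.7 (97.5 - 90.7) and 1 at 0.8 (99.5 - 98.4). Part of that comes from replacing an omnibus test by one contrast.

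These sizes rest on 19 per arm, d = 0.8 at both later visits, equal correlations, normal data and two-sided .05. The correlation is unknown. The reading that pre stays a response level once it is a covariate is the literal one, but the article does not address the case explicitly.

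A reader might infer that results from this plan would be invalid. The documents do not support that: the type I error of each procedure is at or below 5%.

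**What to change.** 1. Remove the baseline significance tests as the trigger for adjustment.
2. For every outcome, always adjust for its own baseline value, with only post and follow-up as response levels. For the continuous outcomes use ANCOVA or a mixed model with group, time, group-by-time, baseline and baseline-by-time. For the mini-BESTest scores, rated 0 to 2 (Outcome measurement), use a baseline-adjusted ordinal or rank-based analysis if a normal model does not suit them.
3. Pre-specify the adjusted AE-LE differences at post and at follow-up, with 95% CIs, as the treatment effects, in place of the omnibus ANOVA plus Tukey. If the average over the two visits is to be the deciding contrast, say so: the 89% to nearly 100% power belongs to that average, and the single-visit ANCOVA figures (73% to 98%) belong to each visit alone.

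The cost is a change of analysis wording and slightly more analysis work. No new data, visits or participants are needed.

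### The Tukey post hoc test fits the 2 × 3 mixed design poorly, and the hypothesis is not tied to the group × time interaction or to an always baseline-adjusted AE minus LE contrast

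*Protocol article*

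**What the plan says.** All of the analysis text is in the Statistical analysis section of the protocol article.

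- **Factors.** "There are two independent variables including the groups (AE vs. LE) and time (pre vs. post vs. follow-up"), so group has two levels and time has three.
- **Model.** A 2 × 3 repeated-measures ANOVA "with group as a between-group factor and time as a within-group factor", fitted to each of seven dependent variables.
- **Baseline.** "If baseline differences of the dependent variables occur, baseline values will be included as covariates". Adjustment is therefore conditional on what the baseline comparison shows.
- **Follow-up tests.** "post-hoc analyses will be conducted using Tukey post hoc test or Mann-Whitney U test". The section does not say which factor or cells Tukey is applied to, or with which error term.
- **Effect size for nonparametric variables.** The "probability of superiority for dependent samples". Whether it describes change within a group or AE against LE is not stated.
- **Alpha.** Set "at .05 for all statistical analyses".

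The hypothesis is in the Problem statement: "participants in an AE group will present greater improvements" than the land group. That is a statement about differential change. The Statistical analysis section does not say which ANOVA effect, or which contrast, tests it.

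**The concern.** The trial's question is whether AE improves more than LE. The answer has to be a between-group comparison of change, or of later values given baseline. The ANOVA yields a group effect, a time effect and an interaction, and the plan does not say that the interaction answers the question.

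The one named parametric follow-up procedure was built for comparing several independent means with a common error variance. Here one factor has only two levels and the other is measured repeatedly on the same people. Depending on how the software is set, the AE versus LE comparison at post could be an ordinary t-test, a very conservative test or a clearly anti-conservative one. That choice would be made at analysis.

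Conditional baseline adjustment adds a second open choice. It also gives up precision whenever the baseline comparison shows no difference, although the baseline value has been measured in any case.

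**Working it through.** The plan gives no figure of its own for this point, and the sample size is not disputed here.

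**Inputs.** From Sample size calculations: 22 per group enrolled, planning values "α = 0.05, and 1-β = 0.80", and an effect given only as d above 0.8, so 0.8 SD is used. *Assumed*, because the document gives none: equal within-person correlation ρ between all pairs of visits, ρ of 0.3, 0.5, 0.7 (and 0.8 for type I error), and the effect patterns below. Tests are taken as two-sided at 0.05.

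**1. Tukey on group (k = 2).** q(0.95; 2, 42)/√2 = 2.0181, and t(0.975; 42) = 2.0181. The two tests are identical. Simulated type I error is 4.9 to 5.3%.

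**2. Tukey on time (k = 3).** In 20,000 null simulations per correlation, the repeated-measures error term under sphericity gives 4.9 to 5.2%. Treating the three visits as independent samples gives 1.6% at ρ = 0.3 and 0.0% at ρ = 0.8.

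**3. Tukey over the six cells, AE versus LE.** The critical value with the within-subject error is q(0.95; 6, 84)/√2 = 2.917. A between-group difference at one visit has variance 2σ²/n, but the within-subject mean square estimates only σ²(1 − ρ). The effective threshold is therefore about 2.917 × √(1 − ρ). At ρ = 0.7 that is 2.917 × 0.548 = 1.60, well below 2.02. Simulated type I error:

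| ρ | Within-subject error, post | Within-subject error, post or follow-up | Pooled cell error, post |
|---|---|---|---|
| 0.3 | 1.7% | 3.2% | 0.4% |
| 0.5 | 4.5% | 8.3% | 0.5% |
| 0.7 | 11.7% | 18.4% | 0.5% |
| 0.8 | 19.6% | 28.0% | 0.6% |

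**4. Power of the candidate tests of the hypothesis, n = 22 per group.**

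*Interaction.* λ = (n/2) Σ(δₜ − δ̄)²/(1 − ρ), on F(2, 84).
- Effects 0/0.8/0.8: Σ = 0.284 + 0.071 + 0.071 = 0.427, so λ = 4.69/(1 − ρ) = 6.70, 9.39, 15.64.
- Effects 0/0.8/0.4: Σ = 0.16 + 0.16 + 0 = 0.32, so λ = 3.52/(1 − ρ) = 5.03, 7.04, 11.73.

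*Baseline-adjusted difference at post.* Noncentrality = 0.8/√[(1 − ρ²)(2/22)(1 + 1/40)] on 41 df; the last factor allows for chance baseline imbalance. This gives 2.75, 3.03, 3.67.

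*Group main effect, effects 0/0.8/0.8.* Noncentrality = 0.533/√[((1 + 2ρ)/3)(2/22)] = 2.42, 2.17, 1.98 on 42 df.

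| Test | ρ = 0.3 | ρ = 0.5 | ρ = 0.7 |
|---|---|---|---|
| Adjusted post contrast (either pattern) | 77% | 84% | 95% |
| Interaction, 0/0.8/0.8 | 62% | 77% | 95% |
| Interaction, 0/0.8/0.4 | 49% | 64% | 86% |
| Group main effect, 0/0.8/0.8 | 66% | 56% | 49% |

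Against the interaction, the adjusted contrast gains 15, 7 and 0 points when the effect persists, and 28, 20 and 9 points when it halves by follow-up.

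**The case against.** The strongest reply is that the plan is already adequate. A hypothesis of greater improvement corresponds to the group × time interaction, which the stated ANOVA delivers, and an informed reader would take it that way. Tukey per visit is a valid t-test, and Tukey on time is valid with the right error term. Error terms and exact contrasts are details that a condensed article may leave to an analysis plan that is not shown here.

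Much of this stands, and it rules out several stronger readings:

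- *That Tukey cannot be used with two groups.* Step 1 shows that it equals the t-test: redundant, not invalid.
- *That Tukey on time uses the wrong error term.* The document states no error term, so this cannot be asserted. The inflated error rates in step 3 likewise belong to one possible reading, not to a stated procedure.
- *That the trial has no valid parametric comparison of AE with LE.* The interaction is one.
- *That power is 49% where 95% was available.* The 49% is for the group main effect, which averages in the pre-test. At the same correlation of 0.7, the interaction has 95%.
- *That the dependent-samples effect size is wrong.* It suits within-group change over time. It is a mismatch only if used to describe AE against LE.

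What remains does not rest on silence alone. The article names a specific post hoc procedure that is redundant or conditional on unstated settings under every reading, and it fixes a conditional rule for baseline adjustment.

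**Conclusion.** The point holds as an improvement to the plan, not as an invalidation of it. The Tukey step adds nothing for group, is correct for time only under conditions not stated, and over the six cells can sit anywhere from about 0.5% to about 20% for AE versus LE at post. The interaction is a valid test of the hypothesis, but the plan does not link the two, and baseline is used only if the groups happen to differ.

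An always-adjusted AE minus LE contrast at post is at least about as powerful as the interaction in every case examined. The gain runs from nothing (ρ = 0.7, sustained effect) to 28 points (ρ = 0.3, effect halving by follow-up).

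These figures rest on assumed correlations and effect patterns, on 0.8 SD, and on all 22 per group contributing. They apply to the post contrast tested first at 0.05, as in a fixed order. Under Holm the smaller p-value would face 0.025 and power would be lower. A fixed order starting at post would also serve poorly if an effect appeared only at follow-up.

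**What to change.** In the Statistical analysis section:

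1. Delete the Tukey step.
2. Replace the conditional baseline rule by adjustment in every case. The pre value then becomes a covariate and is no longer one of the outcome occasions.
3. Name the test of the hypothesis, for example:

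> For each dependent variable, post and follow-up values will be analysed in one repeated-measures model with group, time, group × time and the baseline value (with its interaction with time) as terms. The hypothesis is tested by the baseline-adjusted AE minus LE difference at post and, if significant, at follow-up. Both differences will be given with 95% confidence intervals.

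4. If neither visit is to take precedence, use Holm across the two times instead of the fixed order.
5. Use an independent-groups probability of superiority wherever AE is compared with LE, and keep the dependent-samples version for within-group change only.

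Keeping the interaction as the named deciding test, followed by per-visit AE minus LE contrasts, would also be defensible, at the loss of power shown above.

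The cost is rewording. The visits, data and sample size are unchanged, and the planned software can fit the model. The change should be recorded before outcome data are compared by group.
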